### Participant timeline {13}

Participant recruitment, enrolment, and allocation will all be targeted for the first 24 h following admission to the ICU. Once admitted, the participants will be monitored and evaluated, through a series of assessments, every day they are in the ICU up until their discharge, or at most, 14 days following ICU admission. A follow-up visit is planned for 6 months post-ICU discharge (Fig. 1).

**Fig. 1 Fig1:**
[figure not shown]
Schedule of enrolment, intervention, and assessments. Arrows represent continuous measurements, and X’s represent an assessment or intervention provided at a specific time point. One asterisk indicates that whenever possible, informed consent will be obtained directly from the patient. If the patient is unable to provide informed consent, we will ask the patients’ relatives and/or an authorized representative for the study consent. Two asterisks indicate that we will ask the patients’ relatives at the earliest possible date, with questions regarding the week prior to arrival at the ICU

### Recruitment {15}

With approximately 4000 patients [32] admitted yearly to the ICU at the University Hospital of Bern (Inselspital), we believe achieving our total sample size of 920 participants over the 3 years for which our study is planned is feasible. All patients admitted to the ICU will be screened for inclusion into the study, by either a registered nurse or a treating physician. Family members will be contacted as soon as possible thereafter. Patients will be recruited every day, including on the weekends.

## Assignment of interventions: allocation

### Sequence generation {16a}

In the enrolment phase, ICU patients will be randomly assigned to either the intervention or the control group with 1:1 allocation, stratified by gender and age. The randomization will be computer-generated and performed in the study database using the Research Electronic Data Capture System (REDCap) (Vanderbilt University, TN, USA). The research team will not be blinded.

### Concealment mechanism {16b}

The allocation sequence will be implemented in the study database REDCap by an independent data manager not involved in the analysis of the study. No other study personnel will have access to the allocation sequence that is stored in REDCap. Allocation of individual patients to their respective intervention group will be revealed to study personnel after the allocation has occurred via the web interface of REDCap.

### Implementation {16c}

The allocation sequence assigning participants to their respective group will be computer-generated. The study team will enrol participants prior to allocation.

## Assignment of interventions: blinding

### Who will be blinded {17a}

The research team will not be blinded after assignment to interventions, nor will any member of the interprofessional team be blinded when carrying out the intervention. However, an independent statistician who will be conducting the interim analysis will be blinded.

Additionally, the analysis of the primary outcome of incidence of delirium, and secondary outcome looking at the duration of delirium, will be done blinded.

### Procedure for unblinding if needed {17b}

Only one person, the independent statistician, is blinded during the intervention period of this study. If required, unblinding could occur after the interim analysis has been conducted.

## Data collection and management

### Plans for assessment and collection of outcomes {18a}

The study starts within 24 h after admission to the ICU. In the enrolment phase, participants will be randomly assigned to either the intervention or the control group, with the intervention beginning as soon as possible following enrolment. Three times a day (between 7:00 am and 7:00 pm) for 30 min, participants in the intervention group will receive the intervention (VR stimulation) applied directly in the bed. The intervention will be included in the daily schedule of the patients. The intervention period ends when the patient is discharged from the ICU or at the latest 14 days after admission to the ICU. Thus, the intervention period depends on the length of stay in the ICU and can vary between participants.

After allocation, incidence and duration of delirium is assessed in three shifts a day. If delirium is diagnosed, the standard ICU delirium therapy (local delirium protocol) will be started, regardless of the participants’ group. VR stimulation will optimally start before this time point. Delirium is assessed using the ICDSC which is a reliable (Cohen’s kappa (*κ*) = 0.60) [33] and specific (95%) [33] tool to detect delirium in ICU patients [5] and was translated into German by Radtke et al. [34]

Assessment of sedation will be done using the Richmond Agitation Sedation Scale which has a reliability of *κ* = 0.91 and a face validity with 81–92% agreement [22, 35]. Consciousness will be evaluated according to the Glasgow Coma Score which was originally found to have a *κ* = 0.66–0.77 for the whole scale, but has since been found to have higher reliability when looking at the eye, motor, and verbal scales individually (*κ* = 0.89, 0.94, and 0.88, respectively) [21, 36]. The validity for the Glasgow Coma Scale, however, remains controversial with some stating that the validity has been well established [37], while others question how the scale is assessed under different conditions such as sedation or intubation [36]. Pain will be assessed using the Numeric Rating Scale with an interrater reliability score of *κ* = 0.71 [23] and the Behavioural Pain Observation Tool which has a *κ* = 0.80 and a content validity index of 0.73–1.0 [24].

Movement and movement patterns will be recorded continuously at 100 Hz for the duration of the participants’ stay in the ICU, with AX3 Axivity (Axivity Ltd., Newcastle upon Tyne, UK) inertial measurement units attached to participant’s hands, legs, and chest and placed under the mattress (Sensing Tex, Barcelona, Spain). To enable accurate interpretation of this data, the participant’s environment will be recorded with a camera. This will allow for the distinction to be made between movements made by the participant and those from the interprofessional team or family members. To maximize the privacy of the participant, the camera will be mounted on the head-end of the bed, so the face of the participant is not visible.

Physiological parameters (e.g. non-invasive arterial blood pressure, heart rate, and respiratory rate) will be monitored by the in-house monitor system of the University Hospital (GE Healthcare, Little Chalfont, UK). Respiration and heart rate will be measured at a frequency of 240 Hz, while the blood pressure will be measured as the median every 2 min. A list of pharmacological agents provided to the participant and disease-related data will be collected via the patient data management system. While movement and physiological data will be recorded continuously throughout the patients’ stay in the ICU, the non-continuous assessments will also be completed at various time points (Fig. 1).

At the earliest opportunity, the participant—or, in the event of incapacity, his/her relatives—will be interviewed by the study team about their health-related quality of life, functionality, and frailty, using the EQ-5D instrument [38], the Functional Independence Measure [39, 40], and the Clinical Frailty Score [41], respectively, 1 week before ICU admission and 6 months post-discharge. The reliability and validity of the three-level EQ-5D, the EQ-5D-3L, is well established; however, the more recently expanded five-level version, the EQ-5D-5L, still lacks proper reliability and validity studies [38]. The Functional Independence Measure has a reliability score of *κ* > 0.85 [42, 43] and a high internal validity [42]. The Clinical Frailty Score has been found to have good reliability [44] and good construct validity [41].

Cognitive impairment will be assessed by the study team before ICU discharge and 6 months post-discharge using the Montreal Cognitive Assessment [45]. The Montreal Cognitive Assessment has a known reliability of *κ* = 0.83 [45] and an established content validity in English and in French [45] and a sensitivity of at least 0.90 [46]. The average survival 6 months post-discharge will be obtained via a central database.

The study ends with a follow-up assessment 6 months after admission to the ICU. The study team interviews the participants during a regular follow-up session at the ICU. During the interview, the EQ-5D-5L, Functional Independence Measure, Clinical Frailty Score, and Montreal Cognitive Assessment will be administered. All assessments will be conducted according to the standard ICU care by trained ICU nurses.

In a final step following the VR intervention, the ICU nurse responsible for the intervention will be asked about the feasibility of applying the intervention, completing the 10-item System Usability Scale [29]. The System Usability Scale has a strong reliability score *κ* > 0.89 [47, 48] and an established construct validity, as well as concurrent validity (*r* = 0.86) [47, 48].

### Plans to promote participant retention and complete follow-up {18b}

Contact will be made with the participants after 3 months within the framework of internal quality assurance. After that, the participant will be contacted in writing and by telephone for the 6-month follow-up. If a participant chooses to discontinue the study, the data collected up to the withdrawal date will be anonymized and used.

### Data management {19}

Smaller datasets and measurements (e.g. length of ICU stay) will be stored in the patient data management system of the University Hospital of Bern (Inselspital). The data will be coded by a member of the study team using an alphanumeric system, and the identifying information deleted from the datasets. Only the remaining continuous data, such as physiological measurements, movement patterns, and camera videos, will be stored in-house on a password-protected computer due to their size.

### Confidentiality {27}

The data files are encrypted and will only contain a univocal alphanumeric code, from which the identity of the participant cannot be gathered. The key (i.e. the list in which a code number is linked to a participant name) will be kept separately from the study data, in a secured cabinet, in the custody of a person who is not involved in the study. In study-specific documents, participants are only identified by a unique participant number.

### Plans for collection, laboratory evaluation, and storage of biological specimens for genetic or molecular analysis in this trial/future use {33}

See above Item 26b, there will be no biological specimens collected.

## Statistical methods

### Statistical methods for primary and secondary outcomes {20a}

Descriptive statistics will be applied to both groups to ensure that they similarly represent the population. Among others, we will be looking at the mean and standard deviation of the age, distribution of the sexes, and frequencies of disease in the two samples.

The difference in the incidence of delirium will be tested with the chi-square proportion test, and the duration will be tested with Welch’s *t* test in subgroups of participants with delirium. The effects of the VR stimulation on physiological parameters will be looked at using statistical methods (e.g. *t* test, linear models). Machine learning techniques will be applied to the movement patterns as means of analysis.

The data will be analysed with MATLAB and the software R. Deviation(s) from the original statistical plan will be granted if the collected data do not allow the planned analysis techniques to be performed (e.g. if the collected data does not meet the prerequisites to apply analysis of variance techniques). In this case, more appropriate statistical methods will be applied (e.g. non-parametric methods), and this choice will be justified and detailed in the respective scientific reports.

### Interim analyses {21b}

A blinded interim analysis will be completed after the inclusion of 100 participants (50 per group). A re-estimation and adjustment of the sample size will be made if necessary. The decision about how to proceed following the results of the interim analysis will be made by the independent statistician conducting the interim analysis, together with the principal investigator.

### Methods for additional analyses (e.g. subgroup analyses) {20b}

Using data from movement patterns from a subgroup of participants (*n* = 100), non-supervised machine learning techniques will be applied to try to train a model to predict the onset of delirium. This subgroup will be used to address the secondary objective aimed to evaluate differences in movement patterns and intensity between the intervention and control group and between participants with delirium and without delirium.

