### Objectives {7}

The primary objective of this randomized clinical trial is to analyse the effect of VR stimulation on the incidence of delirium after admission to the ICU. Participants in the control group will receive the standard ICU care, while participants in the intervention group will additionally receive VR stimulation. We hypothesize that participants receiving the VR stimulation will have a lower incidence of delirium during their stay in the ICU, compared to the control group. The secondary objectives are to evaluate differences in movement patterns and intensity between the intervention and control groups and between participants with delirium and without delirium. We expect that these differences will be related to the different types of delirium (i.e. hyperactive, hypoactive, or mixed). Additionally, it is predicted that it will be possible to detect differences in movement patterns between groups and identify patterns indicating the presence or absence of delirium. Secondary objectives also include the evaluation of the effect of VR on duration of delirium. In this case, it is hypothesized that the duration of delirium will be shorter in participants receiving the VR stimulation compared to those in the control group.

Further objectives which will be addressed include (1) evaluating the effect of VR stimulation, identified by changes in physiological parameters; (2) evaluating how easily the VR stimulation can be provided to patients by critical care professionals; (3) describing differences in cognition, health-related quality of life, and functional independence between groups, using questionnaires; and (4) evaluating if VR reduces the need for pharmacological treatment of delirium.

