### Intervention description {11a}

The intervention for this study consists of relaxing VR stimulation, which will be started as soon as possible after obtaining informed consent. As stimulation material, immersive 360-degree videos (e.g. nature environments, animals, urban parks) will be played inside a commercially available head-mounted display, with the video sound played inside noise-cancelling headphones. A single video will be shown during each stimulation period, with each video lasting 30 min in length; however, the length may be shortened based on individual participant reaction. The stimulation will be provided three times per day, morning, midday, and evening, every day until the patient is discharged from the ICU, or the maximum of 14 days has been reached. A new video will be played during each stimulation. A total of 44 videos were filmed. All videos shown on the same day will depict the same location, but at different time points. The location shown on a given day is randomly assigned. Videos filmed in the morning, midday, or evening will be shown in the morning, midday, or evening, respectively.

The intervention group will also receive standard ICU care and, if needed, receive treatment for delirium (local delirium protocol), same as in the control group. Therapy would include pharmacological agents (e.g. quetiapin) and non-pharmacological interventions (e.g. early mobilization, communication tools, sleep improvement, family involvement). The first 100 participants, regardless of their group, will additionally be equipped so data can be recorded regarding movement patterns.

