### Outcomes {12}

The primary outcome is delirium incidence, measured three times a day (morning, midday, and evening) by the Intensive Care Delirium Screening Checklist (ICDSC) as part of standard assessment. With the ICDSC, delirium is determined by consciousness, inattention, disorientation, hallucination, agitation or retardation, speech and mood, sleep/wake cycle disturbance, and fluctuation [19]. A unique incidence of delirium is counted once a patient reaches a score of ≥ 4, on a scale from 0 to 8 [20]. The entire period that a patient has a score ≥ 4 is considered as a single episode, and accordingly, counts only as a single incidence. The mean incidences of delirium per group will be looked at. The incidence of delirium is considered to be clinically relevant as it is known that patients who experience delirium while in critical care have worse long-term outcomes [4]. Furthermore, due to the possible influence of sedatives and analgesics on the incidence of delirium, both sedation and pain levels will be assessed every 2 h [5]. Consciousness and sedation will be measured using the Glasgow Coma Scale [21] and the Richmond Agitation Sedation Scale [22], respectively, and pain will be measured using the Numeric Rating Scale [23] and the Behavioural Pain Observation Tool [24].

As a secondary outcome, the duration of delirium will be evaluated per 8-h periods, or as needed, while patients are in the ICU. If the participant is assessed as delirious via the ICDSC during any of the assessments during an 8-h span, the entire period will count as delirious. Duration of delirium is clinically relevant knowing that the duration of delirium is an independent predictor of mortality 6 and 12 months post-ICU admission [25, 26].

Additional secondary outcomes include the pattern and intensity of movements, before and during delirium as well as between groups, measured continuously during the ICU stay. The fact that patients in delirium have fluctuating motor performance movement patterns, differing from baseline, could be a possible marker for delirium detection [27]. Therefore, acceleration will be measured with wearable sensors such as inertial measurement units, which have been previously used successfully in the ICU [28]. The monitoring of patients’ movement patterns could provide a means of early detection of delirium, permitting early intervention by the care staff.

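### The movement analysis commits to unsupervised learning to predict delirium onset, but onset is a labelled event and no step that trains or tests on the label is stated

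*Protocol article*

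**What the plan says.** The section on additional analyses {20b} gives the method and its purpose in one sentence: in the movement subgroup, "non-supervised machine learning techniques will be applied to try to train a model to predict the onset of delirium". The next sentence assigns the same subgroup to the secondary objective to "evaluate differences in movement patterns and intensity between the intervention and control group and between participants with delirium and without delirium". The main statistics section {20a} is less specific: "Machine learning techniques will be applied to the movement patterns as means of analysis".

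The Objectives {7} expect that the trial can "identify patterns indicating the presence or absence of delirium". The Background and rationale {6a} lists movement analysis, as a source of indicators of delirium, as the second of the trial's two main aims.

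On the data, the Intervention description {11a} states: "The first 100 participants, regardless of their group, will additionally be equipped so data can be recorded regarding movement patterns". The section on assessment {18a} adds: "Movement and movement patterns will be recorded continuously at 100 Hz for the duration" of the ICU stay. Under Outcomes {12}, delirium is "measured three times a day (morning, midday, and evening) by the Intensive Care Delirium Screening Checklist (ICDSC"), and a score of 4 or more on the 0 to 8 scale counts as delirium.

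**The concern.** Predicting the onset of a defined event is a supervised problem. The model is fitted to examples marked as followed, or not followed, by the event, and is judged by how well it separates them in patients it has not seen. An unsupervised method looks for structure in the movement signal without those marks. The structure it finds may relate to coming delirium, but it may equally reflect sedation, nursing care or time of day, and nothing in the fitting steers it one way or the other.

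At stake is whether the sensor substudy can deliver what it is justified by, namely early detection of delirium. If the step that ties movement to the ICDSC is settled only after the data are seen, in 100 patients, there is room to pick whichever clustering happens to line up with delirium. The result would then be hard to read as evidence of prediction.

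**Working it through.** The article states no figure for this analysis beyond the subgroup size of 100, which has no stated derivation, so there is no plan figure to reproduce. The check is mainly a comparison of sections.

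1. **Aim.** Section {20b} wants a model that predicts onset. The Objectives want patterns tied to the presence or absence of delirium. Both are defined by delirium status.

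2. **Label.** Outcomes {12} supplies that status for every participant: ICDSC of at least 4, assessed three times a day. First onset can be read from these scores to within one assessment interval.

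3. **Predictors.** Section {18a} supplies continuous movement recording during the ICU stay, so movement before onset is available for anyone not delirious when recording starts. Outcomes {12} itself refers to movement before as well as during delirium.

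4. **Method.** Section {20b} names only the unsupervised class for the prediction task. It mentions neither fitting to the ICDSC nor testing against it.

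5. **Does {20a} repair this?** It refers to machine learning in general. That neither contradicts nor overrides the specific sentence in {20b}. The deviation clause in {20a} applies when the collected data do not allow the planned technique. The mismatch here is visible before any data exist, so the clause does not cover it.

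6. **Would a supervised analysis have events to learn from?** Inputs are the assumed delirium proportions in Sample size {14} (39% control, 30% intervention) and, as an assumption, a 50/50 split of the first 100, in line with 1:1 allocation:

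   - Expected participants with delirium: 50 × 0.39 + 50 × 0.30 = 19.5 + 15.0 = 34.5.
   - Using instead the 35% to 80% prevalence range quoted in the same section: 100 × 0.35 = 35 to 100 × 0.80 = 80.

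   Usable onsets will be fewer, because the Discussion notes that some patients become delirious soon after admission. The article does not say how many.

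7. **Share of recording taken up by VR, one arm only** (inputs from {18a}: three 30-minute sessions between 07:00 and 19:00):

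   - 3 × 30 = 90 min a day.
   - 90 / 1,440 = 6.25% of a 24-hour recording.
   - 90 / 720 = 12.5% of the 12-hour daytime window.

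   Both are upper bounds, since {11a} and {11b} allow sessions to be shortened or stopped.

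**The case against.** The best defence is that unsupervised methods are not useless for this purpose. Outcomes {12} argues that movement in delirium departs from the patient's baseline. Detecting such a departure is a recognised unsupervised task, and its alarms can be checked afterwards against the ICDSC to give sensitivity and specificity. Unsupervised features can also feed a later predictor. Section {20a} does not restrict the type of machine learning, the second sentence of {20b} includes a comparison by delirium status, and the prediction itself is worded as an attempt. Much of this stands. A reader might infer that the stated method cannot predict delirium at all, and the documents do not support so absolute a claim. What remains is that the article commits to a class of method for prediction without stating the label-based step on which each of these routes depends. That is a stated choice, not a detail left to an analysis plan.

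A reader might also infer that VR sessions contaminate the movement data and confound the comparisons. The documents do not support this either. Nothing says that VR time is kept in a prediction model or that arm is ignored, and such handling is commonly left to the analysis plan. For the comparison between arms, the groups are randomised and a movement difference is itself an objective, so movement during VR is part of the intervention's effect and not a confounder. At most, in a delirium model that pools the arms, session-related movement could be associated with both arm and delirium status, because sessions occur only in the arm assumed to have less delirium.

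**Conclusion.** The point holds as a mismatch between stated method and stated aim. Section {20b} assigns unsupervised learning to a prediction task whose outcome is already labelled, and states no training or testing on that label. It affects the movement subgroup of 100 and a secondary objective that belongs to one of the two main aims. It does not affect the primary outcome, its analysis or the sample size of 920. No plan figure changes. The estimate of about 34.5 participants with delirium rests on the protocol's assumed rates and an even split, and serves only to show that labels would be available. The point is worth correcting before the analysis begins because the remedy is cheap and the label-based step would then be fixed in advance.

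**What to change.** Amend {20b} to say that a supervised or semi-supervised model will be trained on ICDSC-defined first onset, using movement recorded before onset in participants not yet delirious, and validated with whole patients held out. Holding out whole patients matters because continuous recording yields many correlated stretches from the same person. Keep clustering or anomaly detection as exploratory feature extraction, and align {20a} with this wording. The choice of algorithm, resampling scheme and performance measures can be left to the analysis plan.

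If only unsupervised methods are to be used, restate the aim as exploration of movement patterns and drop the claim to predict onset.

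Optionally, and for the pooled delirium model only, add a sensitivity analysis that excludes VR-session windows or includes arm. The randomised comparison of movement between arms needs no such exclusion and should not be described as confounded by VR.

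The cost is a change of analysis wording. The article already plans the ICDSC scores and sensor recordings. The optional sensitivity analysis would set aside at most 6.25% of a full day's recording in the intervention arm, with no extra data collection.
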